### 2.3. Eligibility Criteria

The inclusion criteria for participation in the project will be: (1) being over 18 years of age; (2) being a BS candidate; (3) presenting anxious or depressive symptomatology (moderate scores on the Beck Depression Inventory-II [46,47] and/or Beck Anxiety Inventory [48,49]) or meeting the criteria for at least one ED (anxiety, mood, and related disorders) on the International Neuropsychiatric Interview (MINI; [50]); (4) speaking Spanish or Catalan fluently; (5) committing to attend the sessions; (6) understanding and accepting the contents of the informed consent, expressed by signing it; (7) having Internet to fulfill the protocol assessments and to participate in the online intervention and (8) agreeing to maintain the prescribed medication (including dosage) if any, during the evaluation period and treatment. If medication stability is not possible, the participant’s data will be treated separately in the analyses.

The protocol also includes one exclusion criteria that may interfere: (1) having a severe condition that would require being prioritized for treatment, so that an interaction between the two interventions cannot be ruled out. These include a severe mental disorder (bipolar disorder, personality disorder, schizophrenia, or an organic mental disorder), suicide risk at the time of assessment, or substance use in the last three months (excluding cannabis, coffee, and/or nicotine).

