## 2. Materials and Methods

This is a pilot study using a repeated single-case experimental design (multiple baseline design) to explore the feasibility and clinical usefulness of a transdiagnostic emotion-based online group intervention (UP) for BS candidates with EDs or subclinical anxious or depressive symptoms attended to in a public mental health service. We have chosen this design for three reasons: (1) the unit of intervention and unit of data analysis is an individual case, specifically a cluster of participants; (2) the case provides its own control for comparison purposes because a number of variables are measured before the intervention and compared with measures during and after the intervention and (3) the variable is repeatedly measured within and across different conditions or levels of the independent variable. Furthermore, and because our main objective is to answer the question “Is the Unified Protocol able to improve the emotional state of people waiting for BS?”, we chose a multiple baseline design to improve experimental control throughout replication, introducing the independent variable at different points in time. The fundamental idea of choosing this type of design is that each of the participants can be their own control group [34].

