The multiple baseline design involves the application of the treatment variable in a staggered way over time, through different observational units. This design is suitable for health services research interventions that are focused on changing patient behavior. This methodology facilitates a systematic comparison of pre-intervention and post-intervention measures [35], and conducting a preliminary assessment of a novel intervention [36]. Like randomized controlled trials (RCTs), the multiple baseline design can demonstrate that a significant change in behaviour has occurred and that is result of the intervention. One of the main limitations is that each participant must show changes only when the intervention is applied, and this issue, at a practical level is complicated, can make it difficult for the researcher to draw clear conclusions about the impact of the intervention. In order to reduce this limitation and improve the internal validity, researchers start treatment at different times across settings, behaviors, or people [37]. The multiple baseline design has advantages over the RCTs because this design requires fewer population groups and communities and they may act as their own controls [35]. In this sense, researchers often use this design with several people at once addressing the issue of external validity [37].

In the present investigation, all consecutive patients who are selected to undergo BS and who present anxiety or depressive symptoms or at least one diagnosis of ED, will be asked to participate. Once inclusion criteria are met (see “Inclusion and exclusion criteria” section), each patient will be randomly assigned to one of the multiple baseline conditions: 8, 12, or 15 evaluation days before the intervention. These multiple baseline conditions have been chosen following the current guides for single-case designs [34,38].

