### 2.2. Procedure

The participants who are referred to the mental health unit for having fulfilled the requirements to be candidates for BS, will be evaluated to see if they meet the rest of the inclusion criteria for this study. In Table 1, it can be seen the selection criteria used to choose the appropriate candidates to receive the BS. These criteria are based on the European Guidelines for Obesity Management in Adults, which indicates that a comprehensive obesity management can only be accomplished by a multidisciplinary obesity management team [44].

Participants’ evaluation and selection will be carried out by the clinical psychologists and psychiatrists of the mental health unit of the Regional Hospital of Vinaròs (Castellón). The clinical psychologists who will participate in this trial will be in charge of collecting all the information from the participants (alphanumeric codes assigned to the participants will be entered to safeguard their anonymity). The coded information will be given to the author [name] to introduce it in the database and then, returned to the center.

Participants who have received the approval for BS by the multidisciplinary health team and also have met the inclusion criteria by the clinician (see “Eligibility criteria” section), will be invited to participate in the study through an informative document. They will also be provided with confidentiality and informed consent documents. After accepting to participate, an email will be sent to participants with a link through which they will be able to complete the pre-treatment evaluation on the Qualtrics survey platform [45]. Then, they will be informed by phone of the experimental condition to which they will have been randomly assigned, which may be 8, 12, or 15 days baseline assessment, and they will then complete online the baseline assessment protocol on the same platform [45]. Randomization to the different baselines will be done with randomizer software (www.randomizer.org). Randomization will be performed by a researcher unrelated to the study using the computer-generated sequence mentioned. In the program, the researcher will generate one set of 60 numbers, which will have a one to three range. Participants will be randomly assigned to the 8, 12 or 15 baseline days.

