The baseline and psychological intervention will be conducted between the period of acceptance for BS and the BS implementation, that last approximately one year in public health settings. The intervention will be carried out in an online group format through the Cisco Webex platform. The UP will be applied in twelve weekly 2-h online group sessions. To comply with the experimental design of the multiple baseline, when each participant completes the baseline evaluation, they will receive the first online session in individual format (to receive the first session in stages), then they will continue with the second session and the rest of the treatment in group format. The content of each session is shown in Table 2. Participants will receive the therapy support manual [11]. The online group will consist of five to eight participants, one therapist ([name]), and one co-therapist ([name]). For ethical reasons, if any of the patients feel uncomfortable during the study with the online group format, they may leave the group and receive individual onsite attention (treatment as usual). In this case, the content and estimated number of sessions will be the same, although the frequency will be stipulated by the mental health unit depending on its possibilities.

The study plans to conduct a follow-up assessment every three months until two years after treatment completion. All follow-ups will be conducted online. Considering the time interval of the baseline, the psychological intervention and the BS procedure, the two first follow-ups (three and six months after intervention) will be conducted before BS, and the rest will be conducted after BS. In addition, at the baseline and during treatment, the participants must fill out an online survey made up of 14 questions that will ask about the intensity of the emotions of happiness, sadness, anxiety, other emotions, difficulties in emotion regulation, body image, and emotional eating. Through this weekly evaluation, we expect to observe how the participants evolve in the different variables throughout the different treatment modules.

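### Criterion 8 sets no medication-stability period before entry, so the remaining response to a recently started or changed drug can be counted as change due to the Unified Protocol

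*Protocol article*

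**What the plan says.** **Medication rule (section 2.3, Eligibility Criteria).** Criterion 8 is "agreeing to maintain the prescribed medication (including dosage) if any, during the evaluation period and treatment". The next sentence begins "If medication stability is not possible" and says that such a participant's data will be analysed separately. The exclusion criterion in the same section looks back three months for substance use. No criterion looks back for prescribed medication.

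**Who is enrolled (sections 2.2 and 2.3).** Candidates need at least moderate depressive or anxious symptoms or a diagnosed emotional disorder. Their evaluation and selection "will be carried out by the clinical psychologists and psychiatrists of the mental health unit".

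**Control (section 2).** The plan relies on within-person comparison: "the case provides its own control for comparison purposes because a number of variables are measured before the intervention". All three randomized conditions receive the intervention and differ only in baseline length: "each patient will be randomly assigned to one of the multiple baseline conditions: 8, 12, or 15 evaluation days before the intervention".

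**Treatment (section 2.2).** "The UP will be applied in twelve weekly 2-h online group sessions".

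**Outcomes and analysis (Table 3, sections 1 and 2.6).** The MINI, BDI-II and BAI are primary outcomes. Table 3 marks them at pre-treatment, post-treatment and follow-ups, with no entry under baseline or treatment. The analyses compare scores across time points within participants and calculate an RCI. The first hypothesis is framed in terms of the RCI.

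**The concern.** The rule fixes a period, and that period runs only forward. Someone who began or adjusted a psychotropic drug shortly before entry meets it by changing nothing afterwards.

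This is a plausible case, because entrants are symptomatic and are assessed by psychologists and psychiatrists. The documents do not say how common it is.

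Part of such a drug's response may still be to come when the pre-treatment questionnaires are completed. With no untreated comparison, that part cannot be told apart from response to the intervention. In the pooled means it is diluted by participants without a recent change. In an individual RCI it is not diluted: the whole remaining response enters that participant's score difference. A recent dose reduction or withdrawal could bias in the opposite direction.

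If the date of the last change is not recorded, the study data will not show afterwards who was affected.

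**Working it through.** The plan states no figure on this point, so there is none to reproduce. The check sets its rules side by side and then illustrates size under declared assumptions.

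**1. Whom the medication rule reaches (section 2.3)**

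| Candidate | Meets criterion 8? | Identified for separate analysis? |
|---|---|---|
| Drug and dose long unchanged, held in study | Yes | Not needed |
| Drug or dose changed during evaluation or treatment | No | Yes |
| Drug or dose changed shortly before entry, then held | Yes | No: no pre-entry period is defined |

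**2. Which outcomes the staggered baseline can protect (Table 3)**

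The daily items are measured in baseline and weekly in treatment, so the multiple-baseline logic applies to them. The MINI, BDI-II and BAI have no baseline-phase measurement. For these, all change after the pre-treatment score falls into one pre-post difference, whatever the baseline length.

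**3. Timing for the daily items**

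From the documents: baseline b = 8, 12 or 15 days, a stagger of 15 − 8 = 7 days at most. Treatment is 12 × 7 = 84 days, so it runs on days 9–92, 13–96 or 16–99.

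Assumed: the drug response is linear and complete L days after the start or change, with L from 14 to 56. The change happened g days before baseline day 1.

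Share of the response falling after treatment starts = max(0, (L − g − b)/L). Example: L = 28, g = 0, b = 8 gives 20/28 = 71%.

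| L (days) | g = 0; b = 8 / 12 / 15 | g = 14; b = 8 / 12 / 15 |
|---|---|---|
| 14 | 43 / 14 / 0% | 0 / 0 / 0% |
| 28 | 71 / 57 / 46% | 21 / 7 / 0% |
| 42 | 81 / 71 / 64% | 48 / 38 / 31% |
| 56 | 86 / 79 / 73% | 61 / 54 / 48% |

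The share ranges from nothing to most of the response. The rest falls in the baseline or before it.

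**4. Illustrative size for the pre-post mean**

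Bias = f × d, where f is the share of recent changers and d is the drug response still to come after the pre-treatment score, in SD. Both are assumed.

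- Low: 0.10 × 0.3 = 0.03 SD.
- High: 0.30 × 0.5 = 0.15 SD.

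Completers expected from section 2.1: 60 × (1 − 0.35) = 39. With assumed pre-post correlation r, the SD of change is √(2(1 − r)), and the test statistic shifts by bias × √39 / √(2(1 − r)).

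- Low, r = 0.5: 0.03 × 6.245 / 1 = 0.19. With no true effect, the two-sided 5% test rejects about 5.4% of the time.
- High, r = 0.7: 0.15 × 6.245 / 0.775 = 1.21. It rejects about 23% of the time.

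**The case against.** **The separate-analysis sentence may reach further.** It is not expressly limited to changes after entry, and a candidate whose drug is still being adjusted could be called unstable. That reading is possible. But stability is tied to no pre-entry period, so the sentence gives no means of finding someone who changed recently and then held constant.

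**A condensed article may leave detail elsewhere.** This is true of many operational details. Here, however, the article states the criterion with its period, its dosage clause and its analysis consequence. The point is about the period it states.

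**Frequency is unknown.** Patients reach the unit because they are surgical candidates, subclinical symptoms suffice for entry, and nothing says drugs are started or adjusted at screening. This stands, and it is why the size cannot be derived.

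**The design has some protection.** A reader might infer that a recent drug change would reproduce exactly the pattern of a flat baseline followed by change, and that the stagger could not reveal it. The documents do not support that. Nothing ties drug response to session 1. In the table above, with L = 28 and g = 0, between 29% and 54% of the response falls within the baseline and would tend to show as a slope. Section 2.6 plans visual analysis of slopes by phase and module. This protection is real for the daily items. It does not extend to the MINI, BDI-II or BAI.

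**It is a pilot.** The Discussion asks for cautious interpretation and for later randomized trials, and a look-back would not remove natural course or regression to the mean. Both are fair. They limit the weight of the point, but this source of bias is cheap to identify.

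**Conclusion.** The concern holds in a limited form. Criterion 8 admits recent changers, the separate-analysis rule does not identify them, and their remaining drug response can be counted as intervention change in the MINI, BDI-II and BAI pre-post comparisons and in the individual RCI. It would go too far to say that it will be: that depends on the share of recent changers and on the drugs' time course, and the documents give neither.

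Under the stated assumptions the pooled bias is 0.03–0.15 SD, and the false-positive rate is about 5.4% to 23%. The upper figure needs the upper-end assumptions together.

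A reader might also multiply an assumed 10–30% share by an assumed response of 4–8 BDI-II points and arrive at 0.4–2.4 points. That gives everyone who changed within, say, eight weeks the full response after entry. If changes are spread evenly over those 56 days and the response is linear over 14–56 days, the average share still to come is L/(2 × 56), or 12.5% to 50%. The range then becomes 0.4 × 0.125 = 0.05 to 2.4 × 0.5 = 1.2 points. Changes clustered at screening would give more, but the documents show no clustering. None of these figures should be read as an estimate for this trial.

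**What to change.** 1. At screening, record for every participant the date of the last start or change of any psychotropic drug.
2. In the separate-analysis sentence of section 2.3, define medication stability so that it also covers a period before the pre-treatment assessment. The length is a clinical decision for the investigators and should be set in advance.
3. Repeat the primary pre-post comparisons and the RCI results without recent changers, and report both versions.
4. Optionally, add the same period to criterion 8 and re-screen candidates who do not yet meet it.

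**Cost.** Items 1 to 3 need one screening field, one sentence and one sensitivity analysis. Under the assumed 10–30% share, the sensitivity analysis would keep about 35 to 27 of the 39 expected completers (39 × 0.9 and 39 × 0.7). It would therefore be less precise and should be read beside the main result.

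Item 4 would delay some entries. Section 2.2 gives a wait for surgery of about one year and places the six-month follow-up before surgery. The longest schedule uses about 99 + 183 = 282 of 365 days, which leaves roughly 83 days at most for deferral. A candidate with an early surgery date might be lost.

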### 2.4. Ethics

All participants who meet the inclusion criteria will sign the personal data protection document before randomization so that they have a notion of whom and for what purpose this study’s results will be used. Participants will be also informed of what the treatment consists of before starting it, as well as the duration and phases of the study (informed consent). Direct participation in the study will be voluntary. Participants will not obtain any financial or material compensation, and their participation will not imply any risk for them. The UP has already demonstrated its efficacy in previous experimental and quasi-experimental studies with different health problems (see “Introduction” section).

Data management will be carried out following the Spanish Royal Decree 1720/2008, of 19 January, which approves the Regulations for the development of the Organic Law 15/1999, of 13 December, on the protection of personal data [51]. The treatment, communication, and transfer of personal data will follow the provisions of the Declaration of Helsinki [52] in Law 14/2007 on biomedical research. As of 25 May 2018, the new legislation on personal data in the EU is fully applicable, specifically Regulation (EU) 2016/679 of the European Parliament and of the Council of 27 April 2016, on Data Protection (GDRP; General Data Protection Regulation). Under the aforementioned legislation, participants can exercise their rights of access, modification, opposition, and cancellation of data, for which they must contact their health professional of reference.

The data collected for the study will be identified by an alphanumeric code, and only the health professionals collaborating in the study will be able to relate these data to the participants and their corresponding medical records. Therefore, the identity of the participants in the study will not be revealed to any person, with exceptions in case of a medical emergency or legal requirement.

The study already has the approval by the Ethical Research Committee of the General University Hospital of Castellón (CEIm; CI/HIP version 1.0 de 20/07/2019). In addition, the protocol study has been registered at https://clinicaltrials.gov/ (6 March 2020; NCT04421443).

### 2.5. Measures

The evaluation protocol will be administered online by Qualtrics survey [45] at five different moments: pre-treatment, baseline, treatment, post-treatment, and follow-ups every three months until two years after the intervention. Assessment instruments will include demographic characteristics (age, sex, education, marital status, and employment status), a diagnostic interview, and well-established questionnaires for both primary and secondary outcomes. Next, the primary and secondary outcomes that will be evaluated at the pre, post-treatment, and follow-up periods will be described, and later the specific measures that will be used for the baseline evaluation and during the treatment will be specified. Table 3 shows the distribution of the measures that will be administered during the study.

#### 2.5.1. Primary Outcomes

Primary and secondary diagnosis according to the DSM-5 criteria will be evaluated with the International Neuropsychiatric Interview (MINI [50]). Subclinical symptoms of anxiety and depression will be evaluated through the Beck Depression Inventory-II (BDI-II [46,47]) and the Beck Anxiety Inventory (BAI [48,49]). The weight gain or loss of the participants will be evaluated through the Body Mass Index (BMI).

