## Abstract

Obesity is currently becoming a serious global public health problem due to its high prevalence and continuous increase. This condition is associated with different physical and mental health problems. The presence of emotional disorders (anxiety, depression and related disorders) among candidates for bariatric surgery is very high and predicts worse physical and psychological results. The present study aims to explore the feasibility and clinical usefulness of the Unified Protocol, a transdiagnostic emotion regulation-based intervention, delivered in an online group format to patients with emotional disorder diagnosis or symptoms, who are waiting for bariatric surgery. We will conduct a pilot study with a repeated single-case experimental design (multiple baseline design) in a public mental health service. The sample will consist of 60 participants, who will be randomized to three baseline conditions: 8, 12 or 15 evaluation days before the intervention. Diagnostic criteria, symptomatology and body mass index are the primary outcome measures, and we will include affectivity, personality, quality of life, body image, eating behavior and surgical complications like secondary measures. An analysis of treatment satisfaction will be also performed. Assessment points will include pre-treatment, baseline, treatment, post-treatment, and follow-ups every three months until two years after post-treatment. The results obtained in this study may have important clinical, social and economic implications for public mental health.

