The specific objectives pursued are: to evaluate adherence to treatment and clinical improvement in the primary and secondary measures after applying the UP and to study its long term clinical usefulness until two years after the intervention. Thus, the main hypotheses proposed for this study are: (1) statistically significant differences (reliable change index; RCI) will be obtained between the scores obtained at the pre-treatment, baseline, and post-treatment on the primary and secondary measures; (2) the improvements obtained after the application of the UP will be maintained in the long term (follow-ups of up to two years); (3) participants in the pilot study will report high adherence rates and high satisfaction scores regarding the treatment delivery format and its components.

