Regarding emotion regulation, it will be assessed using the Difficulties in Emotion Regulation Scale (DERS [60,61]), which presents five dysregulation dimensions: emotional lack of control, emotional rejection, life interference, lack of emotional attention, and emotional confusion. In addition, to assess the different emotion regulation skills that will be trained through the UP, we will use the Brief Experiential Avoidance Questionnaire (BEAQ [62,63]), which is a self-report questionnaire with 15 items that measure experiential avoidance; the Philadelphia Mindfulness Scale (PHLMS [64,65]), which is a 20-item questionnaire that assesses two mindfulness constructs: awareness and acceptance and the Emotion Regulation Questionnaire (ERQ [66,67]), which is a self-report questionnaire commonly used to assess two emotion-regulation strategies: cognitive reappraisal (six items) and expressive suppression (four items).

To assess surgical complications, the professional will be asked to refer the participant to the mental health unit a report describing the course of the operation and the recovery from it. Specific measures related to eating disorders will also be used, such as the Bulimic Investigatory Test (BITE [68,69]), which is a self-report questionnaire used to evaluate the presence and severity of bulimic symptomatology, and cognitive and emotional signs and symptoms associated with binge eating; the Body Satisfaction Questionnaire (BSQ [70,71]), which is a self-applied scale used to evaluate the fear of gaining weight, feelings of low self-esteem because of one’s appearance, the desire to lose weight, and body dissatisfaction, and Emotional Eating Scale (EES [72]), which is a 25-item self-report assessing a person’s tendency to cope with negative affect through eating. Participants’ weight will be checked monthly to calculate their body mass index (BMI).

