### 2.6. Data Analysis

The analyses will be carried out with the statistical package IBM SPSS Statistics version 22.0 for Windows [78]. First, the sociodemographic characteristics of the sample will be analyzed with descriptive statistics, calculating the mean and standard deviation of the scores in the different questionnaires administered. Next, a missing-value analysis and the Little Missing Completely At Random (MCAR) test will be performed to determine whether or not the distribution of missing values is random, and therefore whether the last observation made (LOCF) can be used. Internal consistency will be explored using Cronbach’s alpha.

As the sample size is expected to be less than 50, the normal distribution of the variables will be verified with the Shapiro–Wilk normality test. Depending on the result of this test, parametric or non-parametric repeated measures analysis will be carried out to verify whether or not the differences in the scores of the variables measured at different times are statistically significant. In case the variables follow a normal distribution, parametric repeated measures analysis will be carried out, specifically the Multivariate Analysis of Variance (ANOVA), and in case the variables do not follow a normal distribution, non-parametric repeated measures analysis will be carried out, specifically the Friedman test. If the repeated measures analysis show statistically significant differences between the evaluation time points, post-hoc comparisons will be carried out to correct the level of significance to avoid increasing the type I error. Thus, regarding adjustment for multiple comparisons, the Bonferroni correction will be carried out in case of having performed parametric analysis, and the Wilcoxon signed rank test in case of having performed non-parametric analysis in the comparison of means. More detailed information on this has been added in the data analysis section, explaining step by step which statistical analyzes will be carried out.

Finally, the Reliable Change Index (RCI), which assesses the clinically significant change obtained to determine in which variables the scores have approached those of the normative sample, will be calculated. A clinically significant change will be considered if the RCI score obtained is equal to or greater than 1.96 [79].

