Another aspect that we consider important to analyze is how the participants change their scores in each of the variables evaluated based on the content addressed each module. For this purpose, a visual analysis of the changes in the scores will be carried out, to see how the slopes change in the different phases of the study (evaluation and treatment), and in the different modules within the treatment. This visual analysis has been used in previous studies [21]. To carry out this visual analysis, the data from 19 questions that the participants will fill in weekly will be used.

Attendance at sessions will also be recorded to calculate the attendance rate, which will be used as an indicator of viability and acceptance of treatment by users. For the same purpose, quantitative and qualitative analyses will be carried out. At the quantitative level, the participants’ evaluation of and satisfaction with the treatment received will be evaluated using an ad hoc designed questionnaire (see “Measures” section). Qualitatively, participants will be asked to answer six main questions about treatment, and their answers will be analyzed by selecting and classifying the information through a segmentation process, identifying key themes and categories of analysis [80].

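### BMI is a primary outcome judged only by differences between time points, and the 8- to 15-day baselines with monthly weighing give it no pre-treatment trend to serve as a control

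*Protocol article*

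**What the plan says.** The Abstract gives BMI primary status: "Diagnostic criteria, symptomatology and body mass index are the primary outcome measures". Section 2.5.1 repeats it: "The weight gain or loss of the participants will be evaluated through the Body Mass Index (BMI"). Section 2.5.2 adds that participants' "weight will be checked monthly to calculate their body mass index (BMI"), and Table 3 lists BMI at pre-treatment, baseline, treatment, post-treatment and follow-ups.

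Three analyses could bear on BMI.

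- **Group test (section 2.6).** Repeated-measures ANOVA or the Friedman test, to "verify whether or not the differences in the scores of the variables measured at different times are statistically significant".
- **Individual test (hypothesis 1, Introduction).** Significant differences by the Reliable Change Index "will be obtained between the scores obtained at the pre-treatment, baseline, and post-treatment on the primary and secondary measures".
- **Visual analysis (section 2.6).** It is meant "to see how the slopes change in the different phases of the study (evaluation and treatment"), but its data are the 19 daily or weekly questions. The item list in section 2.5.3 covers emotions, regulation, mindfulness, avoidance, emotional eating and body image. It has no weight or BMI item.

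There is no untreated arm. Section 2 says that each participant acts as their own control, with baselines of 8, 12 or 15 evaluation days. The UP then runs for twelve weekly sessions, and the 3- and 6-month follow-ups are expected to fall before surgery (section 2.2).

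**The concern.** A multiple-baseline design replaces a control group with a pre-intervention series. A change counts as an effect when the series departs from its own earlier course at the staggered start of treatment. That can work for items rated every day. It cannot work for a variable measured about once a month against a baseline of at most 15 days.

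For BMI, then, the design reduces to an uncontrolled before-after comparison, although BMI carries primary status and the article presents the design as able to show that change results from the intervention. If weight is falling during the wait for reasons unrelated to the UP, a significant pre-to-post fall would be reported as clinical usefulness. If weight is rising, a real benefit could be missed.

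**Working it through.** **1. Sample available.** The plan enrols 3 × 20 = 60 and assumes 35% loss: 60 × 0.65 = 39 completers. This agrees with the expectation in section 2.6 of fewer than 50.

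**2. Weighings inside the baseline.** With a month of 30.4 days, the expected number of monthly weighings is:

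- 8 days: 8 / 30.4 = 0.26
- 12 days: 12 / 30.4 = 0.39
- 15 days: 15 / 30.4 = 0.49

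At most one monthly weighing falls in any baseline, and one weight gives no slope. The stagger between the shortest and longest baseline is 15 − 8 = 7 days, shorter than the weighing interval.

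**3. Most favourable reading of Table 3.** Suppose every participant has one weight at pre-treatment and one at the end of baseline, 8, 12 or 15 days apart. Assume a within-person BMI SD (s) of 0.2 to 0.4 kg/m², which the documents do not give.

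- A two-point slope over b months has variance 2s²/b². Averaged over the three baselines and divided by 39, the standard error (SE) of the mean pre-UP slope is 0.13 to 0.26 kg/m² per month.
- The treatment slope, from weights at 0, 1, 2 and 2.76 months, has SE 0.015 to 0.031.
- The minimum detectable slope change is 2.8 × the combined SE: 2.8 × √(0.131² + 0.015²) = 0.37, up to 2.8 × √(0.261² + 0.031²) = 0.74 kg/m² per month.

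Over the 2.76 months of treatment, 0.37 per month amounts to 0.37 × 2.76 = 1.02 kg/m². This is optimistic, because between-person variation in slopes is ignored. With an assumed 3-month run of monthly weights before the UP, the detectable change would be 0.06 to 0.12 per month. The pre-UP slope is therefore the limiting quantity.

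**4. What background drift does to a pre-post test.** Assumptions: zero UP effect, mean BMI 42, SD of change 2.0, n = 39, two-sided 5% paired t-test (38 df, critical value 2.024). The noncentrality is (42 × p / SD) × √39, where p is the background fall.

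| Background fall | BMI change | SD of change | Noncentrality | Chance of a significant fall |
|---|---|---|---|---|
| 1% | 0.42 | 2.0 | 1.31 | 25% |
| 2% | 0.84 | 2.0 | 2.62 | 72% |
| 3% | 1.26 | 2.0 | 3.93 | 97% |
| 2% | 0.84 | 1.5 | 3.50 | 93% |
| 2% | 0.84 | 2.5 | 2.10 | 53% |

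With no drift, the total rejection rate is 5%.

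**5. A second parameterisation.** Take a constant drift over the mean interval of 11.7 days plus 12 weeks, (84 + 11.7) / 30.4 = 3.15 months. At n = 39, falls of 0.05, 0.1, 0.2 and 0.3 kg/m² per month give rejection in 16%, 48%, 97% and 100% of trials with SD of change 1.0, and 10%, 25%, 72% and 97% with SD 1.5.

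**6. The opposite direction.** A true UP fall of 2% against a background gain of 1% leaves a net fall of 1%. By the first row of the table, it would be detected in 25% of trials, not 72%.

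**The case against.** **Is weight already changing?** A reader might infer from the multidisciplinary setting that weight is already falling. The documents do not say so. The statement that "a comprehensive obesity management can only be accomplished by a multidisciplinary obesity management team" explains the guideline behind the surgical selection criteria; it does not describe care given alongside the UP. The Introduction's remark on multidisciplinary work before and after surgery is general, and the Discussion's mention of weight loss before surgery describes what the intervention might help to achieve. Table 1 also lists failed dietary attempts as a criterion, which weakens a presumed fall. All of this stands. The point needs only that drift in either direction cannot be excluded and that the design has no means to see it.

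**Would the monthly weights support a trend analysis?** A reader might also infer that the plan ignores trend data it already collects. It does not: step 2 shows that study weights alone hold no pre-UP trend. Clinic weights from before enrolment would be needed. The BMI limits in Table 1 imply at least one such weight, but the documents do not give their number or timing, and it may lie close to pre-treatment. A slope change therefore cannot safely be made the sole BMI result.

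**Is the point already covered?** The study is a pilot, and the Discussion asks for cautious interpretation and later randomised trials. The expected directions in Table 4 do not name BMI. Section 2.3 treats participants with unstable prescribed medication separately. These soften the consequence but do not remove it. Hypothesis 1 still claims significant change on the primary measures, the general caution is not tied to BMI, and the medication rule does not reach diet or other weight care.

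**Is this left to an analysis plan?** The choice of model could be. But section 2.6 already fixes the BMI inference as a time-point comparison and limits the slope analysis to the 19 questions.

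**Conclusion.** The point holds in this form: a pre-to-post BMI difference in this study cannot be attributed to the UP, because the own-control property claimed for the design does not exist for a variable weighed monthly against baselines of 8 to 15 days. That rests on the documents and simple arithmetic.

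The size of the resulting error is conditional. Mean BMI, SD of change and rate of drift are all assumptions. Across the ranges tried, the chance of a significant BMI fall with no UP effect runs from 10% to 100%, against 5% in total without drift. The lower end belongs to a drift of 0.05 kg/m² per month, so even slight drift matters somewhat. If weight is stable during the wait, there is no bias, but the study could not show that it was stable.

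This should be corrected. It concerns the interpretation of one primary outcome and does not undermine the feasibility aims.

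**What to change.** 1. In section 2.6, state that pre-to-post BMI change before surgery is reported descriptively with a 95% CI and is not taken as evidence of UP efficacy. Bring the BMI part of hypothesis 1 into line.
2. As a supportive analysis, where clinic weights from before enrolment exist in the record, combine them with the monthly study weights in a linear mixed model with a change in slope at session 1, restricted to the period before surgery. Report the slope change with its 95% CI and the number of participants with enough earlier weights. If too few have them, say so and leave the descriptive result to stand alone.
3. Record any concurrent weight-management care and show the BMI results with and without those participants.

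The first step is a wording change. The second needs record retrieval, which the collaborating professionals can do because section 2.4 allows them to link study codes to medical records, and one further model. The downsides are irregular earlier weights, an interval wider than that for the simple pre-post change, and a weaker claim for BMI.
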